## Abstract

**Background:**

Compulsivity is a cross-disorder trait underlying phenotypically distinct psychiatric disorders that emerge in childhood or adolescence. Despite the effectiveness of serotonergic compounds in the treatment of obsessive-compulsive disorder, treatment-resistant symptoms remaining in 40 to 60 % of patients present a pressing clinical problem. There are currently no medications that effectively treat the core impairments of autism spectrum disorder. There is an urgent need for the development of conceptually novel pharmacological strategies. Agents targeting glutamate neurotransmission, such as memantine, represent promising candidates. This proof-of-concept clinical study will allow pilot-testing of memantine for both clinical effectiveness and tolerability/safety. Memantine is an *N*-methyl-D-aspartate receptor antagonist, approved for the treatment of Alzheimer’s dementia in a number of countries.

**Methods/Design:**

This 12-week study has an add-on, randomised, double-blind, placebo-controlled design of treatment with memantine, including an up-titration phase (forced flexible dose design, 5–15 mg/day), in patients aged 6–17 years and 9 months with obsessive-compulsive disorder or autism spectrum disorder.

It is planned to include patients with obsessive-compulsive disorder (*N* = 50) or autism spectrum disorder (*N* = 50) across four centres in three European countries. Patients will be randomly assigned to memantine or placebo in a 1:1 ratio. Primary objectives are the investigation of the effectiveness of memantine in paediatric patients for improving symptoms of compulsivity (primary outcome measure: total score on the Children’s Yale-Brown Obsessive-Compulsive Scale) and to explore its tolerability and safety. Secondary objectives are to explore the effects of memantine at the level of structure, function and biochemistry of the fronto-striatal circuits, and to collect blood for genetic analyses and biomarkers. Tertiary objectives are to explore the role of new candidate genes and pathways for compulsivity by linking genes to clinical phenotypes, response to treatment, neurocognitive test performance, and key structural and functional neuroimaging measures of the fronto-striatal circuits and to explore biomarkers/proteomics for compulsivity traits.

**Discussion:**

This study is part of the large, translational project TACTICS (http://www.tactics-project.eu/) that is funded by the European Union and investigates the neural, genetic and molecular factors involved in the pathogenesis of compulsivity. Its results will provide clinically relevant solid information on potential new mechanisms and medication treatment in obsessive-compulsive and autism spectrum disorders.

**Trial registration:**

EudraCT Number: 2014-003080-38, date of registration: 14 July 2014.

## Background

Compulsivity is a cross-disorder trait underlying phenotypically distinct psychiatric disorders that emerge in childhood or adolescence. Compulsivity is defined as the repetitive, irresistible urge to perform a behaviour, the experience of loss of voluntary control over this intense urge, the diminished ability to delay or inhibit thoughts or behaviours, and the tendency to perform repetitive acts in a habitual or stereotyped manner [1]. Obsessive compulsive disorders (OCD) are characterised by repetitive thoughts, impulses or images (obsessions) and repetitive behaviours or mental acts (compulsions) [2] and typically have onset in late childhood or early adolescence and mid-adulthood [3, 4]. Autism spectrum disorders (ASD) are characterised by persistent deficits in (1) social communication and social interaction across multiple contexts, and by (2) restricted, repetitive patterns of behaviour, interests or activities. ASD have their onset prior to age 3 years, and a strong persistence over time in childhood, over adolescence and into adulthood [2].

This study is part of a large, translational project funded by the European Community's Seventh Framework Programme (FP7/2007-2013) under grant agreement number 278948, TACTICS (Translational Adolescent and Childhood Therapeutic Interventions in Compulsive Syndromes). It aims to identify the neural, genetic and molecular factors involved in the pathogenesis of compulsivity (http://www.tactics-project.eu/).

### Compulsivity and compulsivity-associated disorders

Compulsivity and the closely associated impulsivity trait are characterised by behavioural disinhibition maintained by maladaptive fronto-striatal brain circuits [5]. Current neuroanatomical models posit the existence of separate but intercommunicating compulsive and impulsive fronto-striatal circuits, differentially modulated by neurotransmitters [5]. In the compulsive circuit, a striatal component (caudate nucleus) may drive compulsive behaviours and a prefrontal component (orbitofrontal cortex, OFC) may exert inhibitory control over them. Increased activity within the striatal components or decreased activity in the prefrontal components may thus result in an increased automatic tendency for executing impulsive or compulsive behaviours, depending on the sub-component affected. Childhood OCD has recently been associated with decreased prefrontal activity [6], fitting with reduced prefrontal control over the striatum. Interestingly, glutamatergic imbalance in fronto-striatal regions has also been observed in childhood OCD [7]. Furthermore, earlier work has shown reduced volume of the striatum in children with ASD that relates to repetitive and compulsive behaviours [8, 9].

### Glutamatergic mechanisms and fronto-striatal circuits

The fronto-striatal circuits implicated in compulsivity and impulsivity are notable for their relatively rich glutamatergic receptor density [10]. Moreover, glutamate modulates the metabolism and function of the fronto-striatal circuits. Glutamatergic projections to and from the various frontal sub-regions (OFC, infralimbic cortex and prelimbic cortex) to the striatum play a key role in the regulation of various compulsive behaviours in humans including: (1) the feeling of loss of control (OCD), (2) repetitive motor behaviours (stereotypy in ASD), and (3) a maladaptive habitual pattern (addiction). Neuroimaging studies have confirmed that glutamatergic projections between the various frontal sub-regions and the striatum play a key role in the regulation of compulsive behaviours in humans ([10, 11]. Compulsivity has been associated with increased glutamatergic activity in the striatum and the anterior cingulate cortex in clinical magnetic resonance spectroscopy (MRS) studies [11].

### Glutamatergic medication in the treatment of compulsivity/impulsivity

Despite the effectiveness of serotonergic compounds in the treatment of OCD, treatment-resistant symptoms remaining in 40 to 60 % of patients present a pressing clinical problem [12–14]. Thus, there is an urgent need for the development of conceptually novel pharmacological strategies. Consistent with the hypothesis of the role of glutamatergic dysregulation in the pathophysiology of OCD, agents targeting glutamate neurotransmission, such as memantine (and riluzole), represent promising candidates (e.g. [13–17]). Open-label studies in children and adults have provided supportive evidence for the effectiveness of these glutamate-modulating compounds for OCD symptoms [12, 13, 18–22]. There are currently no drugs that have been shown to effectively treat the core impairments of ASD. Although studies of serotonin reuptake inhibitors and atypical antipsychotics have suggested improvement of repetitive behaviour in ASD, this has yet to be proven in placebo-controlled trials [23–25]. Emerging evidence from neuroimaging studies suggests: individuals with ASD show an imbalance of excitatory (glutamate) and inhibitory neurotransmitters (gamma-aminobutyric acid (GABA)). Such regionally specific abnormalities in glutamatergic neurotransmission may vary across the lifespan [26, 27]. Ghanizadeh reviewed investigations of amino acid levels in plasma, serum and cerebrospinal fluid (CSF) from ASD patients and reported both increased levels of glutamate and homocysteine and decreased levels of glutamine and tryptophan [28].

### Systematic literature review and choice of investigational compound

A systematic literature review (Mechler et al., in preparation) has recently been performed within the TACTICS network, in preparation for this exploratory ‘Glutamatergic medication in the treatment of Obsessive Compulsive Disorder and Autism Spectrum Disorder’ (GOAT) trial. It focused on the evaluation of glutamatergic substances with potential benefit for the treatment of paediatric patients in multi-centre studies aiming at compulsivity-related disorders. In summary, there were a total of 21 trials (paediatric randomised controlled trials and open-label trials). Six substances were evaluated: D-cycloserine, memantine, minocycline, modafinil, *N*-acetylcysteine, and riluzole. The most substantial information appeared to be available for the compound memantine. Memantine is an *N*-methyl-D-aspartate (NMDA) antagonist, clinically used as a ‘cognitive enhancer’, regulatory-approved for the treatment of Alzheimer’s dementia in a number of countries. It has successfully been used and further been studied in children diagnosed with ASD for the treatment of cognitive, behavioural, and memory dysfunctions, in open-label and controlled trials [29–31]; cf. a recent clinical development program (memantine) sponsored by Forest Laboratories/Merz Pharmaceuticals, www.clinicaltrials.gov). Memantine has also been explored for the treatment of attention deficit/hyperactivity disorder (ADHD) (e.g. [32]). However, additional research examining the efficacy/effectiveness and tolerability/safety of memantine, e.g. placebo-controlled clinical trials, is needed. Findings on memantine suggested clinical effectiveness in ASD and OCD symptomatology and appeared to offer the best risk-benefit profile for multi-centre trials with paediatric patients suffering from compulsivity-related disorders. Considering the current state of knowledge and assessing available findings on effectiveness, tolerability/safety and feasibility of study implementation, the subgroup of experts in paediatric psychopharmacology from the TACTICS consortium jointly decided to apply the compound memantine for this paediatric pilot study.

### Molecular-genetic factors involved in compulsivity, in ASD and OCD

Compulsivity-related disorders such as OCD and ASD are assumed to be highly heritable but genetically complex, with multiple genetic variants of small effect contributing to disease in most patients [33]. Genes encoding the SLC1A1, SLC1A2 and SLC1A3 glutamate transporters are candidate genes for both OCD and ASD [34]. Genes encoding the NMDAR1 [35] and NMDAR2A [36] subunits of the postsynaptic NMDA glutamate receptor are associated with ASD and those encoding the NMDAR2B subunit with paediatric OCD [37]. Novel approaches are needed to facilitate the identification of genetic risk factors for brain disorders and related traits, like compulsivity. One such approach is the study of intermediate phenotypes [38]. It has been shown that using intermediate phenotypes indeed did improve the chance of establishing significant findings in genetic studies [39–41].

### Biomarkers – proteomics of compulsivity and associated disorders

Symptoms of compulsivity-associated disorders such as OCD, ASD and ADHD frequently co-occur in the same patients [42]. Quantitative and molecular genetics, cognitive and imaging studies indicate that this clinical overlap is due to common genetic factors and/or common underlying neural and molecular mechanisms (review, see [43]). Indeed, it has been shown that alterations in brain development, mitochondrial function, immune system and oxidative stress pathways as well as dysfunctions in neurotransmitter systems may be involved in several or all of these disorders [44–47]. The biological determinants that contribute to the pathogenesis of these conditions, however, are poorly defined, and currently, no well-characterised biomarkers are available. One major positive impact of this study – as integral part of the TACTICS project – may lead to a greater insight into the molecular mechanisms involved in the development of compulsivity and compulsivity-associated disorders and potentially facilitate the development of much needed differential diagnostics, improved drug discovery and clinical development, and designs based on biomarker-based segmentation of patients. This may allow for earlier diagnosis and personalised medicine strategies for more effective treatments in the future [48–51].

### Aims and objectives

#### Primary objectives

To investigate: clinical effectiveness of the glutamatergic compound memantine in paediatric patients with OCD (GOAT-1) and ASD (GOAT-2) with respect to symptoms of ‘compulsivity’ (assessed as total score of the Children’s Yale-Brown Obsessive-Compulsive Scale (CY-BOCS; [52])) and to explore tolerability and safety (based on, e.g. laboratory measures, electrocardiography (ECG), adverse events) of the compound memantine in these clinical indications.

#### Secondary objectives

To explore: the effects of glutamatergic interventions at the level of structure, function and biochemistry of the fronto-striatal circuits (magnetic resonance imaging (MRI), MRS), in subgroups (e.g. disorders, age range).

To collect: blood for genetic analyses and biomarkers.

To explore: additional clinical outcomes, disorder-specific outcomes (e.g. core symptoms, response rates, social functioning).

#### Tertiary objectives

To explore: the role of new candidate genes and pathways for compulsivity by linking genes to clinical phenotypes, neurocognitive test performance, and key structural and functional neuroimaging measures of the fronto-striatal circuits.

To explore: biomarkers/proteomics for compulsivity traits.

## Methods/design

This study is a multi-national, multi-centre, randomised, double-blind, parallel, placebo-controlled add-on trial with three study periods: study period I will be a 2-week screening (and washout) period, study period II will be a 12-week double-blind, randomised, placebo-controlled period, and study period III will be a double-blind 1-week down-titration period. Study medication (memantine or placebo) will be added to regular treatment for the respective disorders. Male and female patients (*N* = 50 per disorder, i.e. OCD, ASD), will be randomised into study period II. Patients who complete study period II will participate in study period III. The study visit intervals (suggested and allowed) for the three study periods are outlined in detail as part of the schedule of events (SOE) (Table 1).

**Table 1 Tab1:** Schedule of events

Study period (SP)	SP I (screening/ washout)		SP II (double-blind treatment)						SP III (down-titration)			
Visit number:	1	2	3	4	5	6	7	8	9	10	Unscheduled visits^a^	Early discontinuation
(End of) week:	−2	−1	0	1	2	4	6	8	12	13		
Suggested time to next visit (days):	7	7	7	7	14	14	14	28	7			
Allowable time to next visit (days):	5–9	5–9	5–9	5–9	10 - 18	10–18	10–18	24–32	5–9			
Clinical assessments:												
Informed consent/assent	X											
Psychiatric assessment	X											
Systematic Interview, e.g. DISC (OCD group)	X											
Systematic Interview, e.g. DISC (re co-morbidities): ODD, CD, tic domains (all patients)	X											
ADI-R short version, (ASD group)	X											
WIS-C (4 subtests)	X											
Inclusion/exclusion criteria	X	X	X									
Randomisation to active drug vs. placebo			X									
Demographics	X											
Physical examination	X											
Medical history	X											
Discontinuation of prohibited medications	X											
Height, weight, vital signs	X								X			X
Clinical laboratory tests^b,c,^	X		X^c^			X			X^c^		(X)^a^	X^c^
Serum and urine pregnancy test^d^	X											
Urine drug screen	X										(X)^a^	X
Urine analysis	X		X			X			X			X
Biomarkers			X									
Genetics			X									
Physical Development Scale			X						X			
CGI-S	X		X	X	X	X	X	X	X	X		X
CGI-I				X	X	X	X	X	X	X		X
C-GAS			X			X			X			X
CBCL, 6–18			X									
CY-BOCS			X	X	X	X	X	X	X	X	(X)^a^	X
Children’s Social Behaviour Questionnaire			X	X	X	X	X	X	X	X	(X)^a^	X
Repetitive Behaviour Scale-Revised (RBS-R),			X	X	X	X	X	X	X	X	(X)^a^	X
CHIP-CE/AE			X			X			X			X
PAERS			X	X	X	X	X	X	X	X	X	X
Neuropsychological test battery			X						X			X
Neuroimaging assessments			X						X			
AE monitoring		X	X	X	X	X	X	X	X	X	X	X
Concomitant medications	X	X	X	X	X	X	X	X	X	X	X	X
Eligibility to remain in study		X	X	X	X	X	X	X	X	X	X	X
Study drug dispensed			X	X	X	X	X	X	X			
Study drug returned				X	X	X		X	X	X		X

^a^laboratory tests, ECG, etc. at unscheduled visits (due to AEs) according to the discretion of the investigator

^b^patients with significant increase after baseline (visit 3) in AST, ALT, total bilirubin, or AP from the upper limit of the lab reference range will have additional lab testing and/or consultation

^c^to be collected in a fasting state at visits 3 and 9 (and early discontinuation, if possible); fasting defined as at least 8 hours with water as the only oral consumption

^d^females of child-bearing potential only; additional pregnancy tests possible at each visit at the discretion of the investigator

*AE* adverse event, *ASD* autism spectrum disorders, *AST* aspartate aminotransferase, *ALT* alanine aminotransferase, *AP* alkaline phosphatase, *CBCL* Child Behaviour Checklist, C-GAS Children’s Global Assessment, CGI-I, Clinical Global Impression-Improvement, CGI-S Clinical Global Impression-Severity, *CHIP-CE/AE* Child Health and Illness Profile, *CY-BOCS* Children’s Yale-Brown Obsessive-Compulsive Scale, *DISC* Diagnostic Interview for Children, *ECG* electrocardiography, *OCD* obsessive-compulsive disorder, *PAERS* Pediatric Adverse Event Rating Scale

### Information and consent procedure

Subjects and their parents will be asked to participate in this study by one of the (sub-) investigators. They will receive a letter/informed consent document explaining the study (in their local language). All children and adolescents will also receive a respective letter/informed assent document about the study, with the (complexity of the) language suitably adapted. After an adequate time interval, the subjects’ parents will be contacted again. If subjects require more time to consider participating, as much time as is necessary will be allowed. Informed consent and assent will be obtained from all guardians and participants before inclusion. If the patients and parents decide to participate, a brief screening will be conducted, e.g. on the telephone, to check for any major exclusion criteria. If after this brief screening the subject is included in the study, they will receive a set of questionnaires at home. Parents will be asked to fill out these forms and return these to the centre.

### Study period I (screening period with washout)

Study period I is a 2-week screening and washout period (visits 1–2); during this period, patients will be screened for study eligibility. Before or at the day of visit 1, the study will be explained to the patient and his or her parent or legal guardian, who will then sign and date the informed consent and assent documents (*International Classification of Diseases* (ICD); as adequate according to the legal requirements in the respective country). The ICD must be signed before any study procedures are conducted and before patients discontinue any excluded medications.

Screening for eligibility begins at visit 1. If the patient is eligible, the patient will enter the washout phase during which all excluded medications will be tapered off and stopped entirely by visit 2 (for the respective compounds, the medication-free period should be at least five half-lives in duration). Randomisation to active drug or placebo will occur at visit 3. At visit 1, patients will undergo psychiatric screening tests and safety screening procedures. A patient history will also be taken. See the study SOE (Table 1) for a complete list of study period I procedures. All criteria for enrolment, including the ECG and laboratory analyses, will be verified prior to randomisation at visit 3. At visits 2 and 3, patients will be further evaluated by the clinical research team as shown in the study SOE (Table 1).

### Study period II (acute period)

Study period II is a 12-week, randomised, double-blind, and placebo-controlled add-on acute treatment period (visits 3–9). At baseline (BL), patients will randomly be assigned to active drug or placebo in a 1:1 ratio. In order to safeguard patients in the study, patients can be either in outpatient or inpatient status. For patients in both the active drug treatment group and in the placebo group, dosage will be given depending on the patient’s weight, and will be up-titrated according to Table 2. Visit 7 will be performed via a telephone interview with assessments of effectiveness and tolerability/safety (no physical examination, ECG, blood draws, etc.); if needed from a clinical perspective ‘unscheduled visits’ will be performed, based on investigator judgment.

**Table 2 Tab2:** Memantine dosing schedule in mg/day by body weight; study period II

	Dose range (mg/day)^a^ of distributed medication at … (for weeks …):					
Screening/Baseline Weight (kg)	V3 (wk 1)	V4 (wk 2)	V5 (wks 3–4)	V6 (wks 5–8)	V8 (wks 9–12) ^b^	V9 (wk 13) (discontinuation)
≥60	5	10	15	15	15	10 → 5 → 0
40–59	5	10	10	10	10	5 → 0
20–39	5	5	5	5	5	5 → 0

Dose titration aims at target doses as indicated in the table, based on clinical judgment.

^a^Dosage may be adjusted upwards and downwards by 5 mg/day increments within the range shown for each weight group at indicated visits/dates

^b^Dose should remain stable during the last 4 weeks of study period II (weeks 9–12), unless a dose reduction is necessary for tolerability or safety reasons, based on clinical judgment

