### Study period III (double-blind down-titration period)

Study period III is a 1-week double-blind down-titration period (visits 9–10) from study medication, active drug or placebo. Any patient who completes study period II (visit 9) will continue into study period III. In a blinded fashion, their dose of study medication will be titrated down depending on their final dose in study period II. Placebo-treated patients from study period II will continue placebo treatment in study period III. In order to maintain the blind, all patients will receive the respective amounts (e.g. number of tablets) of study drug (active or placebo). The final visit of this period will be visit 10. See the SOE for the timing of events and the measures to be assessed (Table 1).

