### Medication and dosing

The investigator or his/her designee is responsible for explaining the correct use of the investigational agent(s) to the patients and parents, verifying that instructions are followed properly, maintaining accurate records of study drug dispensing and collection, and of returning all unused medication at the end of the study.

This study involves a comparison of an active drug (memantine) with matching placebo. During study period II, medication will be initiated and modified according to the weight group of the patient at BL (visit 3). Dosing may then be increased (or decreased) by 5 mg/day increments, respectively, at specified visits/dates according to the weight of the subject (cf. Table 2). Stepwise up-titration is recommended to the target dose or the highest tolerable dose by week 4, accordingly. Dosing should remain stable during the last 4 weeks of study period II unless a dose reduction is necessary for tolerability or safety reasons. In case of dose-adjustments due to AEs unscheduled visits can be performed (for stepwise down-titration). Patients who cannot tolerate the minimum daily dose specified (5 mg/day) will be discontinued from the study. Investigator decisions on dose changes (up or down) will only be permitted at study visits (or, due to AEs, at unscheduled visits for down-titration). Study medication will be given once daily in the evening, with or without food.

Based on the dosing information from the published literature and considering earlier and ongoing trials with memantine (sponsored by the pharmaceutical company Forest Laboratories, Berlin, Germany) in this age group, dosing was chosen weight-based, accordingly, also taking into account dose-unit availability in Europe (see Table 2).

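### Patients who cannot tolerate 5 mg/day are taken out of the study, not just off the drug, so no week-12 CY-BOCS is collected; the Table 2 taper also needs a minor correction

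*Protocol article*

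**What the plan says.** **Intolerance of the lowest dose.** The rule is in Medication and dosing: "Patients who cannot tolerate the minimum daily dose specified (5 mg/day) will be discontinued from the study". It applies in every weight band. Table 1 marks CY-BOCS at visits 3 to 10 and in the early-discontinuation column. The Statistical analysis section places the primary endpoint at the end of the treatment phase, which is visit 9, week 12. It names LOCF and MMRM as examples of methods to use if drop-out is high, and adds sensitivity analyses.

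**Week-13 taper.** The rows of Table 2 are screening/baseline weight bands. The column heading says the doses are those "of distributed medication at" each visit, and the last column is "V9 (wk 13) (discontinuation". Table 1 marks "Study drug dispensed" at visit 9. For the same week, Study period III says: "their dose of study medication will be titrated down depending on their final dose in study period II". Final doses below target are permitted:

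- Footnote a of Table 2: "Dosage may be adjusted upwards and downwards by 5 mg/day increments within the range shown for each weight group at indicated visits/dates".
- Footnote b asks for a stable dose in weeks 9 to 12 "unless a dose reduction is necessary for tolerability or safety reasons, based on clinical judgment".
- Medication and dosing: "Stepwise up-titration is recommended to the target dose or the highest tolerable dose by week 4, accordingly".

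**The concern.** The main issue is the difference between stopping the drug and leaving the trial. A child who cannot take 5 mg/day can still be rated at week 12, and the visits are already scheduled. The rule ends those visits, so the primary outcome goes uncollected because of something that happened on treatment. If memantine and placebo differ in tolerability, the loss differs by arm, and the patients left at week 12 are no longer the two groups that were randomised. This is fixed when the data are collected: an analysis plan can choose how to model the gap but cannot supply the rating.

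The lesser issue is that two parts of the article use different keys for the same taper. For patients of 60 kg or more who finish below 15 mg/day, including those whose dose was lowered for tolerability, the only numbers printed in their row are for a different final dose. That matters for dispensing and safety in week 13, not for the efficacy comparison.

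**Working it through.** The article gives no drop-out rate and no power calculation, so there is no stated figure to reproduce. The check sets the schedule and the dosing table against the rules.

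**1. What is observed after removal for intolerance**

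Inputs: visit weeks and CY-BOCS marks from Table 1; endpoint at week 12 from Statistical analysis.

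Gap = 12 − week of the exit rating, if the exit falls at a scheduled visit:

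| Exit at visit | Week | Weeks before the endpoint |
|---|---|---|
| 4 | 1 | 12 − 1 = 11 |
| 5 | 2 | 12 − 2 = 10 |
| 6 | 4 | 12 − 4 = 8 |
| 7 | 6 | 12 − 6 = 6 |
| 8 | 8 | 12 − 8 = 4 |

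What happens to the week-12 value depends on the method:

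- LOCF: the exit rating stands in for week 12.
- MMRM: week 12 stays missing; the patient contributes only the ratings up to exit, under a missing-at-random assumption.
- General linear model on observed week-12 changes: the patient drops out of the analysis.

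None of the three has an observed week-12 score for this patient.

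**2. Weight of one patient**

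Inputs: 50 per diagnosis (Study population), 1:1 allocation (Randomisation).

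- Within a diagnosis: 50 / 2 = 25 per arm, so one removal is 1 / 25 = 4% of that arm.
- Both diagnoses together: 100 / 2 = 50 per arm, so one removal is 1 / 50 = 2%.

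**3. Printed taper against permitted final doses**

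Inputs: Table 2 and footnote a. Change at the first step = first printed week-13 dose − final period II dose.

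| Weight band | Final dose (mg/day) | Printed taper | First-step change |
|---|---|---|---|
| ≥60 kg | 15 | 10 → 5 → 0 | 10 − 15 = −5 |
| ≥60 kg | 10 | 10 → 5 → 0 | 10 − 10 = 0 |
| ≥60 kg | 5 | 10 → 5 → 0 | 10 − 5 = +5 |
| 40–59 kg | 10 | 5 → 0 | 5 − 10 = −5 |
| 40–59 kg | 5 | 5 → 0 | 5 − 5 = 0 |
| 20–39 kg | 5 | 5 → 0 | 5 − 5 = 0 |

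A zero first step is not in itself the fault. At 5 mg/day, the smallest tablet supplied, holding and then stopping is a sensible taper. The fault is that one final dose has two printed tapers. After 10 mg/day it is 10 → 5 → 0 in the heaviest band and 5 → 0 in the middle one. After 5 mg/day it is 10 → 5 → 0 in the heaviest band and 5 → 0 in the other two. A taper keyed to final dose cannot do that.

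**4. Are the two points linked?**

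No. Only patients who complete period II enter the taper, so those removed for intolerance before visit 9 never reach it.

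**The case against.** **On removal from the study.** This is a pilot that disclaims confirmatory analysis, the missing-data methods are left open, and sensitivity analyses are promised. That lowers the stakes but does not answer the point: comparing the arms on CY-BOCS is still the first primary objective, and the loss occurs before any method is chosen.

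A reader might infer that the exit rating replaces the week-12 score. The article does not say so. That follows only under LOCF; otherwise the week-12 score is simply missing.

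A reader might also take Benefits and risks assessment to allow only two responses to an adverse event, dose adjustment or leaving the study. Its wording introduces these as examples, so it does not establish that. The explicit rule under Medication and dosing carries the point.

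It is fair to add that Withdrawal of individual subjects separately allows removal for urgent medical reasons. Changing the intolerance rule leaves that provision in place.

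**On the taper.** A reader of Table 2 alone might infer that the protocol raises the dose of a patient of 60 kg or more who finishes on 5 mg/day. The documents do not support this. Study period III says the dose goes down and depends on the final dose, and Table 2 describes its doses as targets subject to clinical judgment. Each printed row fits a patient who finishes on target, and the steps needed for lower doses can be read from the other rows. Nor would such an increase be hidden by the blind, which conceals drug against placebo; the investigator sets the dose level. What stands is that the printed numbers and the governing sentence disagree for a permitted group of patients.

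**Conclusion.** The main point holds as a cheap improvement. A stated rule, not an omission, ends follow-up for patients who cannot tolerate 5 mg/day, leaving their last CY-BOCS 4 to 11 weeks short of the endpoint if they leave at visits 4 to 8. Each one is about 4% of an arm within a diagnosis, or 2% of an arm overall. The number of such patients, any imbalance between arms and the resulting bias cannot be sized from the article. That the loss may differ by arm is a reasonable possibility, not a demonstrated fact.

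The taper point is minor. It concerns permitted final doses of 10 and 5 mg/day at 60 kg or more, where the printed row, read alone, gives no reduction and a 5 mg/day increase respectively. Study period III already rules out the increase. Since the taper begins after the week-12 assessment, the primary endpoint is not affected; only week-13 dosing and the visit 10 ratings could be.

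**What to change.** **Follow-up after intolerance**

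- In Medication and dosing, replace the end of the sentence on intolerance of 5 mg/day by: *will stop study drug and keep the scheduled visits through visit 9, including CY-BOCS, unless consent or assent is withdrawn.*
- In Benefits and risks assessment, change the example of leaving the study early to stopping study drug early.
- In Study period III, add that patients already off drug do not enter the week-13 taper. Without this, a child who stopped drug but attended visit 9 could be read as having completed period II and be sent into a down-titration with nothing to titrate.

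Cost: a few visits for patients no longer on drug, and off-drug CY-BOCS values that the analysis must say how to handle. The visits already stand in Table 1.

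**Taper column in Table 2**

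| Final period II dose (mg/day) | Week 13 |
|---|---|
| 15 | 10 → 5 → 0 |
| 10 | 5 → 0 |
| 5 | 5 → 0 |

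Add: *No week-13 dose exceeds the final period II dose.* Cost: one table column and one sentence. The 5 and 10 mg tablets already supplied cover every sequence; sites dispense at visit 9 by final dose instead of by weight.
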